### The Primary Endpoint

It will comprise mortality rates and complications (allcause death, acute
myocardial infarction, stroke, renal failure, acute respiratory distress
syndrome and bleeding reoperation) occurring within 30 days of surgery. Hospital
mortality is defined as death occurring within 30 days after surgery. Myocardial
infarction is defined as the appearance of a new Q wave on the electrocardiogram
with an increase of CKMB> 100 IU/L and/or> 10% of the total CK level
and/or new wall movement abnormalities, with the exception of the septum,
documented on the echocardiogram. Neurological complications are defined as
stroke (neurological deficit> 24 hours with positive findings on computed
tomography) or transient ischemic attack (neurological deficit <24 hours with
positive findings on computed tomography). Renal insufficiency is defined as an
increase in plasma creatinine> 2 associated with a urinary output <0.5 mL
kg/h/in 12 hours. Acute respiratory distress syndrome (ARDS) is defined as the
presence of tachypnea (respiratory rate> 30 breaths/min), bilateral pulmonary
infiltrate on chest radiography, severe hypoxemia (arterial oxygen partial blood
pressure/inspired oxygen fraction <200), the need for positive pressure
end-expiratory flow> 5 cmH2O, no evidence of left ventricular failure (wedge
pulmonary capillary pressure <18 mmHg), and no pathological features to
explain these findings. Reoperation for bleeding is defined as the need to chest
reopening in the presence of> 500 mL of blood by the chest tube within the
first hour, >400 mL within the second hour, >300 mL within the third hour,
or total bleeding >1000 mL within the fourth hour.

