**Methods:**

FRAGILE is a two-arm, parallel-group, multicentre, individually randomized
(1:1) controlled trial which will enroll 630 patients with blinded outcome
assessment (at 30 days, 6 months, 1 year, 2 years and 3 years), which aims
to compare adverse cardiac and cerebrovascular events after off-pump
*versus* on-pump CABG in pre-frail and frail patients.
Primary outcomes will be all-cause mortality, acute myocardial infarction,
cardiac arrest with successful resuscitation, low cardiac output
syndrome/cardiogenic shock, stroke, and coronary reintervention. Secondary
outcomes will be major adverse cardiac and cerebrovascular events, operative
time, mechanical ventilation time, hyperdynamic shock, new onset of atrial
fibrillation, renal replacement therapy, reoperation for bleeding,
pneumonia, length of stay in intensive care unit, length of stay in
hospital, number of units of blood transfused, graft patency, rate of
complete revascularization, neurobehavioral outcomes after cardiac surgery,
quality of life after cardiac surgery and costs.

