### Statistical Analysis

The sample size of the FRAGILE trial was based on the ability to detect a 40%
reduction in the primary outcome in the off-pump group compared with the on-pump
group, assuming an event proportion after on-pump CABG of 20.8% and accepting a
risk of type I and II error of 5% and 20%, respectively, and a crossover rate of
5%^[24]^. Consequently,
at least 630 patients will be enrolled.

All of the data will be analyzed according to intention-to-treat
(*i.e.*, based on treatment allocation). Therefore, we will
report treatment-received analyses according to the intervention actually
received. Baseline characteristics and operative characteristics will be
compared with the use of chi-square test, t-test, or Kruskal-Wallis test, as
appropriate. Dichotomous data will be presented as numbers and percentages.
Continuous data will be presented as mean and standard deviation or median and
interquartile range. The continuity corrected chi-square test will be used for
comparison of the 30-day endpoint. Mantel-Haenszel chi-square tests will be used
to adjust for study-center effects. Treatment effects at 30 days will be
expressed as OR and 95% CI. For the 12-month endpoint, Kaplan-Meier curves will
be constructed, and the study groups will be compared with use of the log-rank
test. HR and 95% CI derived from the Cox proportional hazards model will be
provided for the composite outcome and individual components. All statistical
analyses will be performed with the use of the R-3.1.2 language for handling and
storage of data and performing of statistical calculations.

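### The Abstract and the Primary Endpoint section state different primary outcomes that share three of six components, and the sample size does not say which list its 20.8% event rate covers

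*Protocol article*

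**What the plan says.** Two parts of the current text define the primary outcome.

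- **Abstract, Methods.** It opens with "Primary outcomes will be all-cause mortality, acute myocardial infarction", continues with "cardiac arrest with successful resuscitation, low cardiac output" and ends with "syndrome/cardiogenic shock, stroke, and coronary reintervention". It lists five times of outcome assessment, "assessment (at 30 days, 6 months, 1 year, 2 years and 3 years), which aims", and does not mark any of them as primary. Reoperation for bleeding is among its secondary outcomes.
- **Methods, The Primary Endpoint.** "It will comprise mortality rates and complications (allcause death, acute", then "myocardial infarction, stroke, renal failure, acute respiratory distress", then "syndrome and bleeding reoperation) occurring within 30 days of surgery". The section goes on to define these components.

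Statistical Analysis sizes the trial on the primary outcome: "group, assuming an event proportion after on-pump CABG of 20.8% and accepting a" 20% type II error, with a 40% relative reduction and a total of 630. It gives a citation for these assumptions and no component list. It then describes a continuity-corrected chi-square test and odds ratio at 30 days, a log-rank comparison at 12 months, and hazard ratios for the composite and its components. It does not refer back to either list.

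**The concern.** The two lists are not a long and a short form of one endpoint. The Abstract adds three components that the endpoint section lacks, leaves out three that it has, and makes one of those three (reoperation for bleeding) secondary. A reader working from the Abstract and a reader working from the Methods would count different patients as having had the primary event, and would test different hypotheses.

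Two things are at stake. First, the primary hypothesis should be fixed before anyone sees results, and with both lists in print a later choice between them cannot be shown to have been made in advance. Second, the power statement is a statement about one event rate. If that rate was taken from a composite other than the one analysed, the stated 80% does not apply to the trial's actual test.

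**Working it through.** **Step 1. Compare the lists.**

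| Component | Abstract | The Primary Endpoint |
|---|---|---|
| Death from any cause | primary | primary |
| Myocardial infarction | primary | primary |
| Stroke | primary | primary |
| Resuscitated cardiac arrest | primary | not listed |
| Low output / cardiogenic shock | primary | not listed |
| Coronary reintervention | primary | not listed |
| Renal failure | not listed | primary |
| Acute respiratory distress syndrome | not listed | primary |
| Reoperation for bleeding | secondary | primary |
| Time window | none singled out | 30 days |

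Three components are shared and three are unique to each list: 3 + 3 + 3 = 9 distinct components.

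**Step 2. Reproduce the planned sample size.** Inputs from Statistical Analysis: on-pump rate p1 = 0.208; 40% relative reduction, so p2 = 0.6 × 0.208 = 0.1248; type I error 5% (two-sided assumed, since the text does not say); power 80%. The 1:1 allocation comes from the Abstract.

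n per arm = [1.960 × √(2·p̄·(1−p̄)) + 0.842 × √(p1(1−p1) + p2(1−p2))]² / (p1−p2)²

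- p̄ = (0.208 + 0.1248)/2 = 0.1664, so √(2 × 0.1664 × 0.8336) = 0.5267
- √(0.1647 + 0.1092) = 0.5234
- p1 − p2 = 0.0832
- n = (1.0323 + 0.4405)² / 0.0832² = 2.169 / 0.006922 = 313.4, rounded up to 314 per arm

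The total is 628, against the stated 630. This leaves out the 5% crossover that the plan mentions, and any continuity correction (with the correction the total is 674). The 630 therefore comes straight from 20.8% against 12.48%.

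**Step 3. What if 20.8% is not the rate for the list analysed?** The documents give no rate for either list, so the on-pump rates below other than 20.8% are assumptions. The 40% reduction, two-sided 5% level and no crossover are kept, with 315 per arm.

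Power = Φ{[(p1−p2)·√315 − 1.960·√(2·p̄·(1−p̄))] / √(p1(1−p1) + p2(1−p2))}

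Example at 15%: p2 = 0.09, p̄ = 0.12. The numerator is 0.06 × 17.748 − 1.960 × 0.4596 = 1.0649 − 0.9007 = 0.1642. The denominator is √0.2094 = 0.4576. Φ(0.359) = 0.64.

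| On-pump rate | Off-pump rate | Power with 630 | Total for 80% power |
|---|---|---|---|
| 15% (assumed) | 9.0% | 64% | 920 |
| 18% (assumed) | 10.8% | 73% | 746 |
| 20.8% (plan) | 12.48% | 80% | 628 |
| 25% (assumed) | 15.0% | 88% | 500 |

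**The case against.** The best reply is that the body of the article can be followed on its own. It has a section with a singular title, a 30-day window and component definitions, and Statistical Analysis provides a 30-day test to match. On that view the Abstract is simply out of line. Much of this stands: a reader might infer that the trial has no usable primary endpoint, and that goes too far. It does not remove the contradiction. The Abstract is current text, and its list is not arbitrary. Its stated aim is to compare adverse cardiac and cerebrovascular events, and its components closely match the outcomes that the Introduction reports for the earlier trial in 341 high-risk patients. Nor is this detail that an article may leave to a fuller document, because two statements conflict and any later document must contradict one of them.

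Other stronger readings also fail:

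- **Inflated type I error from several primary tests.** The Abstract's plural might suggest six separate primaries, or a test of both lists. No section plans either. The body speaks of one primary endpoint and one composite.
- **The lists favour different arms.** The Discussion does cite a trial with fewer bleeding reoperations and less acute kidney injury off-pump, but that trial's composite, which included new renal failure, did not differ significantly. The Introduction mentions more repeat revascularization off-pump in some reports, but also no significant difference in reintervention in the high-risk trial. The direction of any tilt is not established.
- **The sample size cannot be reproduced, or 20.8% is wrong.** The arithmetic does reproduce, if crossover is left out. The source of the rate is only cited, so one can say that the text does not assign it to a list, not that it belongs to the wrong one.
- **Reoperation for bleeding is double-counted in the body.** Secondary Outcome Measures lists it at 180 days, a different window from the 30-day primary. The conflict over its status lies between the Abstract and the endpoint section.

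**Conclusion.** The point holds as an internal contradiction about what the trial tests, and it must be settled before analysis. Half of each six-component list is missing from the other, and only one list has a time window. The 80% power is conditional on 20.8% being the on-pump rate for the list finally analysed, and the article does not establish that.

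The power range of 64% to 88% illustrates this dependence over assumed on-pump rates from 15% to 25%; it does not estimate the trial's actual power. It rests on a two-sided 5% test without continuity correction, a constant 40% relative reduction and no crossover. How the stated 5% crossover enters the sample size is a separate question and does not affect this conclusion.

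**What to change.** Before any outcome data are analysed:

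1. Reconcile the Abstract with The Primary Endpoint and declare one primary composite at one time point. The list in The Primary Endpoint is the natural candidate, because its components are defined and its window matches the 30-day test in Statistical Analysis.
2. Rewrite the Abstract to match, including the status of reoperation for bleeding, and report the components found only in the Abstract as secondary outcomes.
3. In Statistical Analysis, name the chosen composite where the sample size is given and state which list the 20.8% refers to. If it is not the rate for the chosen list, restate the rate and the resulting power.

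Steps 1 and 2 change wording only. Step 3 is also only wording if 20.8% is confirmed. If the rate proves lower, the sponsor has to accept less power or reopen the sample size (on the assumptions above, 920 patients at 15%), which is a reason to settle it early.

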### Data Storage, Follow-Up and Outcome Measures

All variables from the study will be stored online through a REDCap Web Platform
(http://www.project-redcap.org/).The REDCap is a secure web application for
building and managing online surveys and databases. REDCap can be used to
collect virtually any type of data, it is specifically geared to support data
capture for research studies. This will be done through national healthcare
card, address and telephone numbers. On the basis of the registers, it will be
collected copies of hospital records and death certificates during the follow-up
period. The neurocognitive tests will be planned in accordance with the
statement of consensus of assessment of neurobehavioral outcomes after cardiac
surgery^[22]^.

We will assess health-related quality of life using the World Health Organization
quality of life questionnaire^[23]^. Neurocognitive and quality of life tests will be carried
out at baseline and at 6 months postoperatively. No follow-up visits will be
planned; however, patients will be routinely seen by the referring cardiologist
1 and 6 months after the operation. Hospital records and death certificates will
be blinded for the allocated treatment and forwarded to 2 randomly selected
members of the adjudication committee, who will assess whether each of the
pre-specified outcomes had occurred. In case of disagreement, the 2 assessments
together with a copy of the record of the event will be sent to a third member,
who will have to select the most likely assessment.

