### Limitations

Some limitations of our trial are to be noted. Firstly, the assessment of graft
patency will not be performed by coronary catheterization (test which indicated
surgery). In contrast, coronary computed tomography angiogram will be performed
in all patients for this purpose. Secondly, the events will not be adjudicated
by a blinded adjudication committee. All data will be provided by the local
investigators according to the protocol definitions.

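### Creatinine and wall-motion criteria in the 30-day primary composite can be read in more than one way, listed and defined terms differ, and the article contradicts itself on who applies them

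*Protocol article*

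**What the plan says.** All definitions below are in The Primary Endpoint section of the protocol article.

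- **Infarction.** The rule opens "infarction is defined as the appearance of a new Q wave on the electrocardiogram", continues "with an increase of CKMB> 100 IU/L and/or> 10% of the total CK level", and ends "and/or new wall movement abnormalities, with the exception of the septum". Nothing groups the conditions.
- **Renal.** The criterion is an "increase in plasma creatinine> 2 associated with a urinary output <0.5 mL" per kg per hour over 12 hours. The 2 has no unit and no stated reference value.
- **Terms.** The composite lists death and then "myocardial infarction, stroke, renal failure, acute respiratory distress" syndrome and bleeding reoperation. The text then defines neurological complications, which are stroke "tomography) or transient ischemic attack (neurological deficit <24 hours with" positive CT, and renal insufficiency. Neither is the listed term.

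On who applies these rules, the article gives two accounts:

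- The Abstract describes outcome assessment as blinded. Data Storage, Follow-Up and Outcome Measures says records will "be blinded for the allocated treatment and forwarded to 2 randomly selected" adjudicators, with a third member choosing between the two assessments if they disagree.
- Limitations says events will not be adjudicated "by a blinded adjudication committee. All data will be provided by the local" investigators, working from the protocol's definitions.

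**The concern.** An article may leave much to the full protocol. Here it prints thresholds for the primary endpoint, and Limitations points back to the protocol's definitions as the rule in use. If a rule has several readings, two people can classify the same patient differently and both be following the text.

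The consequence depends on who does the classifying. Assessors masked to allocation would mainly add noise: more or fewer events than planned, some power lost, and a composite that is hard to compare with other trials. Assessors who know the allocation could resolve doubtful cases differently by arm, which would bias the comparison.

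**Working it through.** **1. Infarction rule.** Let Q = new Q wave, E1 = CK-MB above 100 IU/L, E2 = CK-MB above 10% of total CK, W = new non-septal wall-motion abnormality. Three groupings fit the words:

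| Reading | Rule |
|---|---|
| A | Q and (E1 or E2 or W) |
| B | (Q and (E1 or E2)) or W |
| C | (Q and E1) or E2 or W |

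Each reading contains the one above it. A and B disagree on every patient with W but no Q. C adds patients with E2 but neither Q nor W. C is strained, because both enzyme thresholds hang on the same phrase after the Q wave. The real choice is between A and B.

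**2. Renal rule.** Let b be preoperative and p peak postoperative creatinine, in whatever unit the 2 is meant.

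- Rise of more than 2: p > b + 2
- Level above 2: p > 2
- More than doubled: p > 2b

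The level reading always includes the rise reading, since b > 0. Doubling is looser than a rise of 2 when b < 2 and stricter when b > 2. It is looser than the level reading when b < 1 and stricter when b > 1. The readings therefore rank differently from patient to patient. Under the level reading, anyone with b > 2 meets the creatinine half before surgery, and Study Population does not exclude chronic kidney disease. The urine-output condition must still be met.

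**3. Terms.** Stroke itself has one definition (deficit over 24 hours with positive CT). TIA appears only under the broader defined term, so the list suggests that it does not count, but the text does not say so. The Abstract's primary outcomes contain no renal item, so the renal rule matters only if the Methods composite governs.

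**4. Illustration of size.** Inputs from Statistical Analysis: on-pump risk 20.8%, 40% reduction (0.6 × 20.8% = 12.48%), 630 patients (315 per arm at 1:1), 5% error (two-sided assumed), 80% power, continuity-corrected chi-square.

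The plan's figure: the uncorrected pooled formula needs 314 per arm, 628 in total, and gives 80.2% power at 315. This agrees with 630 only if the stated 5% crossover is left out, which is a separate matter.

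With the correction, power = Φ((d − 1/n − 1.96·SE0)/SE1), where SE0 and SE1 are the pooled and unpooled standard errors. At plan: d = 0.0832, 1/n = 0.0032, SE0 = 0.0297, SE1 = 0.0295, giving Φ(0.74) = 77.1%.

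Assume that looser readings add the same number of percentage points to both arms:

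| Points added | Risk ratio | Power, uncorrected | Power, corrected |
|---|---|---|---|
| 0 | 0.60 | 80.2% | 77.1% |
| 2 | 0.635 | 76.6% | 73.3% |
| 5 | 0.68 | 71.9% | 68.5% |
| 10 | 0.73 | 65.7% | 62.3% |

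Now assume no true effect, a risk of 16.64% (the mean of the two planned risks), and labelling that differs by β between arms. SE = √(2 × 0.1664 × 0.8336 / 315) = 0.0297. The rejection rate is P(|Z + β/SE| > 1.96 + c/SE), with c = 1/315 for the corrected test and 0 otherwise:

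| β (points) | Uncorrected | Corrected |
|---|---|---|
| 0 | 5.0% | 3.9% |
| 1 | 6.3% | 5.0% |
| 2 | 10.3% | 8.5% |
| 3 | 17.3% | 14.7% |

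One point is about 3 patients per arm (0.01 × 315 = 3.15).

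**The case against.** The strongest reply is that most of this has a natural reading. The enzyme thresholds qualify the Q wave. TIA is not on the list. The word increase weighs against a level above 2, and low urine output is also required, so a raised baseline creatinine alone cannot make an event. This stands in part. Enzyme-alone infarction and TIA are weak as ambiguities. It does not supply the creatinine unit or reference, or settle wall motion without a Q wave.

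A reader might infer that unblinded local investigators will decide the events. The article does not support that as a settled fact. Two places describe blinded assessment, and Limitations denies blinded adjudication without saying that local investigators know the allocation. For a surgical comparison that is a fair inference, but still an inference.

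A reader might also infer that differences between sites bias the result. Randomization is stratified by centre and Mantel-Haenszel tests adjust for it, so a site's reading applied equally to both arms does not in itself bias the comparison.

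Finally, the added points and labelling differences are assumed, as is their neutrality to treatment. The 10-point case would add nearly half of the planned on-pump risk, and with the corrected test a 1-point labelling difference does not take the error rate above 5%. All of this stands, so the tables show sensitivity and are not estimates.

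**Conclusion.** The point holds as one of indeterminate wording in the primary endpoint. The creatinine criterion and the place of wall-motion change in the infarction rule each allow readings that give different event counts. Listed and defined terms need aligning; the TIA part is the weakest.

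The consequence turns on an unresolved contradiction. If Limitations governs, labelling could differ by arm. If the Data Storage section governs, the harm is mainly noise and lost power, because a third adjudicator who picks between two assessments does not supply the missing logic.

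The documents give no component or misclassification rates, so the effect cannot be sized from them. On the assumed ranges and the planned test, power falls from 77% to between 73% and 62%, and labelling differences of 1 to 3 points give false-positive rates of about 5% to 15%, against 3.9% with none. The change is worth making before events are classified. Nothing here shows that the comparison will be biased.

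**What to change.** 1. The sponsor states its intended reading: bracket the infarction rule so that it is explicit whether wall-motion change counts without a Q wave; give the creatinine unit and define the criterion against the patient's preoperative value; use the same terms in the list and the definitions, and say whether TIA counts.
2. Reconcile the Abstract, the Data Storage section and Limitations into one assessment process, and state whether assessors know the allocation. Make the Abstract and Methods composites agree, so that it is clear whether the renal item is primary.
3. Record the raw elements in REDCap (ECG, CK-MB, total CK, echocardiogram, preoperative and peak creatinine, urine output, duration of deficit, CT) and derive each component by one written rule, blind to arm, in place of the local label.

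Cost: protocol wording, a few data fields and one derivation program. The downside is a slightly longer case report form. Any later statement about power or error rate should use the continuity-corrected test and label its misclassification rates as assumptions.

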### Secondary Outcome Measures

Major adverse cardiac and cerebrovascular events after OPCAB and CABG
in pre-frail and frail patients (1 year)Major adverse cardiac and cerebrovascular events after OPCAB and CABG
in pre-frail and frail patients (2 years)Operative time (180 days)Mechanical ventilation time (180 days)Hyperdynamic shock (180 days)New onset of atrial fibrillation (180 days)Need for pacing >24 hours (180 days)Renal replacement therapy (180 days)Reoperation for bleeding (180 days)Pneumonia (180 days)Length of stay in intensive care unit (180 days)Length of stay in hospital (180 days)Transfusion requirement (180 days)Graft patency assessed by coronary computed tomography (1 year)Correlation between clinical and angiographic scores to prognosis (1
year)Recurrence of angina (1 year)

